### 6.3 Clinical Study Supply, Dispensing and Accountability

All study vaccines will be provided by DLS/designated party to the study site. The Investigator will acknowledge receipt of the study vaccines indicating shipment content and condition. All study vaccines used in the study will be accounted for in the "Study Vaccines Accountability Record" provided by DLS/available at study site", which indicates the date of administration to the subject.

Temperature (between +2°C and +8°C) will be monitored during the shipment. The Investigator will check the temperature record and store it in the Site TMF. The Investigator shall inform the Sponsors immediately of any shipment temperature out of the range. The Investigator must maintain an inventory record of study vaccine received and administered. At the end of the clinical trial, all study vaccines will be returned to EVI/ICGEB or designee, including study vaccines used and/or not administered to subjects. A shipment log identifying each vial will be included in the shipment. In case a vial of vaccine is broken or unusable, the vaccine manager should replace it with a replacement vaccine vial. Although the Sponsor need not be notified immediately in these cases, documentation of the use of the replacement vial and reason for using it must be recorded by the Investigator on the vaccine administration page of the CRF and on the "Study Vaccines Accountability Record".

At the conclusion of the clinical trial and as appropriate during the course of the clinical trial, the Investigator will return all used and unused study vaccines, packaging, labels, and a copy of the

*Information contained in this publication is the property of EVI and ICGEB and is confidential and will not be disclosed to third parties without written authorization from EVI and ICGEB. No part of this document may be reproduced, stored in a retrieval system or transmitted in any form or by any means -electronic, mechanical, recording or otherwise - without the prior authorization of EVI and ICGEB*

[figure not shown][figure not shown]

completed vaccine accountability ledger to the monitor or to DLS/appropriate designee at the address provided in the Investigator folder at each site.

## **6.4 Method of Assigning Subjects to Vaccination Groups**

### **6.4.1 Subject Numbering**

Each subject is usually uniquely identified in the study by a combination of his/her centre number and subject number. Upon signing pre-screening informed consent form, the subject will be assigned a screening number. Once assigned to a subject, a subject screening number will not be reused. Only if the subject tests negative for anti-malarial antibodies, he will be administered the main informed consent form. Following the signing of the main informed consent, further study-related procedures will be undertaken. Similarly, the subject will be assigned a randomisation number once he fulfils all the eligibility criteria. If the subject fails to be randomised for any reason, the reason for not being randomised will be entered on the appropriate pages of the CRF.

### **6.4.2 Screening Number**

The pre-screening informed consent form will be administered to the subject following which the subject will be assigned a unique screening number. This number will be alphanumeric of length 4. The first digit of this number will be S, and the next three digits identify the subject and will be assigned sequentially, with 001 corresponding to the first subject pre-screened/screened. Thus, study subjects will get screening numbers like S001, S002 and so on. The informed consent process for the main study using the main informed consent form will be conducted at the clinic following which the same unique screening number assigned to the subject will be used. Thus, the same number will be used to identify the subject both during the pre-screening as well as the screening period.

### **6.4.3 Randomisation Number**

All subjects eligible after screening will undergo a complete physical examination and evaluation of medical history. A complete review of inclusion/exclusion criteria (including laboratory assessments) will be conducted. Provided all the inclusion criteria and no exclusion criteria are met, subject will be enrolled into the study and will be assigned a unique randomisation number.

The randomisation number will be a three-digit subject number and will be cohort specific. The first digit identifies cohort as 1 (Cohort 1), 2 (Cohort 2) or 3 (Cohort 3), and the next two digits identify the subject within cohort and will be assigned sequentially as per the enrolment. Thus, study subjects in Cohort 1 will get randomisation numbers like 101, 102 and so on sequentially, study subjects in Cohort 2 will get randomisation numbers like 201, 202 and so on sequentially and study subjects in Cohort 3 will get randomisation numbers like 301, 302 and so on sequentially.

### **6.4.4 Adherence to Randomisation List**

The Investigator will designate separate appropriately qualified personnel as the “vaccine manager” and the “vaccinator” respectively. The vaccine manager will be a qualified and trained individual, who will be exclusively dedicated to vaccine preparation while the “vaccinator” will be an independent physician/nurse, who will be responsible for administration of the assigned vaccine as indicated in the randomisation list for the individual subject.

*Information contained in this publication is the property of EVI and ICGEB and is confidential and will not be disclosed to third parties without written authorization from EVI and ICGEB. No part of this document may be reproduced, stored in a retrieval system or transmitted in any form or by any means -electronic, mechanical, recording or otherwise - without the prior authorization of EVI and ICGEB*

[figure not shown][figure not shown]

Only the subject will be blinded during the conduct of this single-blind study. Since the study and control vaccines can be distinguished by their appearance, the vaccine preparation area and the vaccine administration area will be physically separated. Also, the syringe barrels will be covered with opaque tape to ensure subject blinding.

Adherence to randomisation list will be verified by the study monitor by checking the randomisation list against the study vaccine administration records at each study visit.

#### **6.4.5 Emergency Unblinding**

The present study is designed as a single-blind study. Hence, only the subjects taking part in the study will not know whether they have been assigned to the investigational vaccine or the control vaccine. The investigators, investigator staff, persons performing the assessments, and data analysts will remain unblinded to the identity of the vaccine and hence unblinding per se is not applicable for this study.

*Information contained in this publication is the property of EVI and ICGEB and is confidential and will not be disclosed to third parties without written authorization from EVI and ICGEB. No part of this document may be reproduced, stored in a retrieval system or transmitted in any form or by any means -electronic, mechanical, recording or otherwise - without the prior authorization of EVI and ICGEB*

[figure not shown][figure not shown]

## 7 STUDY CONDUCT, ASSESSMENTS AND VISIT PROCEDURES

### 7.1 General Aspects

This is a phase I, randomised, controlled, dose-escalating, single-blind clinical study for assessment of the safety and immunogenicity of the JAIVAC-1 – Montanide ISA 720 in healthy Indian male subjects between 18 to 45 years of age.

There are two (2) discreet informed consent documents for this study. Following the signing of the pre-screening informed consent form, each subject will be assigned a unique screening number. Thereafter, the required blood sample for testing for anti-malarial antibodies by ELISA will be drawn. Only if the subject tests negative for anti-malarial antibodies, he will be further administered the main informed consent form.

Following the signing of the main informed consent for the actual study participation, the relevant study related activities and screening procedures will be undertaken. The subject's demographic data, medical history and concomitant medication history will be recorded at screening/baseline. All subjects included in screening will undergo a detailed physical examination (including vital signs) as well as all protocol-defined laboratory assessments for the screening period (D-14 through D-1).

Informed consent process will include counselling about birth control measures for male subjects by the Investigator team. Results of HIV, Hepatitis B, and Hepatitis C virus infection will be reported in a confidential manner to the study subject only and will not be reported to anyone outside of the study.

A complete review of inclusion/exclusion criteria will be conducted and subjects in whom all inclusion criteria and no exclusion criteria are met, will be enrolled in the study if in good health as judged by physical examination and medical history and will be given a unique randomisation number.

The protocol-defined screening period is 14 days. In case, a subject exceeds this defined screening period (D-14 through D-1), then the subject will have to be re-screened keeping the same screening number. This subject will undergo all the screening procedures again prior to eligibility check and study entry; however the previously done pre-screening procedures and the pre-screening as well as main informed consents will be considered valid at the time of this re-screening. Apart from this, no retest for any abnormal laboratory parameters reported during the screening period will be allowed.

There will be three (3) cohorts in this study corresponding to the three (3) dosages of the investigational vaccine being evaluated. Following enrolment, the first 15 eligible subjects will be randomised and assigned to either the investigational vaccine arm (JAIVAC-1 – Montanide ISA 720 vaccine, n= 10 subjects) or the control vaccine arm (Hepatitis B vaccine, n= 5 subjects) of the Cohort 1 in a ratio of 2:1 respectively, both administered as a 3-dose schedule. Subsequent 15 subjects will be assigned to Cohort 2 and the last 15 subjects will ultimately be a part of Cohort 3 in a similar randomisation ratio of 2:1.

*Information contained in this publication is the property of EVI and ICGEB and is confidential and will not be disclosed to third parties without written authorization from EVI and ICGEB. No part of this document may be reproduced, stored in a retrieval system or transmitted in any form or by any means -electronic, mechanical, recording or otherwise - without the prior authorization of EVI and ICGEB*

[figure not shown][figure not shown]

Thus, dosing of the JAIVAC-1 – Montanide ISA 720 vaccine will begin with Cohort 1 (i.e. 0.1 ml (10 µg each antigen) of investigational vaccine administered by intramuscular route as a 3-dose schedule, followed by Cohort 2 (i.e. 0.25 ml (25 µg each antigen) of investigational vaccine) and finally Cohort 3 (i.e. 0.5 ml (50 µg each antigen) of investigational vaccine). Each cohort will be staggered into sub-cohorts such that the subjects in each cohort will be enrolled over a three day period. The first three (3) subjects of the first dose (Cohort 1) will be kept under observation for 24 hrs following vaccination. The decision of the 24-hour housing for the remaining subjects will be jointly taken by the Principal Investigator and Medical and Safety Monitor, DLS.

Dose escalation to a higher dosage of JAIVAC-1 – Montanide ISA 720 will occur after review of safety data by the DSMB through Day 14 after the first vaccination for all subjects in a cohort. In each cohort, each subject will receive a total of three (3) doses of either of the study or control vaccines by intramuscular route, one each on Day 0, Day 28 and Day 180 respectively. Thus, overall 30 subjects will receive JAIVAC-1 – Montanide ISA 720 (10 subjects for each cohort) and 15 subjects will receive control vaccine, Hepatitis B vaccine (5 subjects for each cohort) as follows:

### Cohort 1

|                      |                                                                                                                                                                                                                                |
|----------------------|--------------------------------------------------------------------------------------------------------------------------------------------------------------------------------------------------------------------------------|
| Test Arm 1    | 10 subjects shall receive dosage A of investigational vaccine (0.1 ml of JAIVAC-1 containing 10µg PfMSP-1 19 and 10µg PfF2 formulated with adjuvant Montanide ISA 720) by intramuscular route on Days 0, 28 and 180 |
| Control Arm 1 | 5 subjects shall receive control vaccine (1 ml of Hepatitis B vaccine) by intramuscular route on Days 0, 28 and 180                                                                                                            |

### Cohort 2

|                      |                                                                                                                                                                                                                                 |
|----------------------|---------------------------------------------------------------------------------------------------------------------------------------------------------------------------------------------------------------------------------|
| Test Arm 2    | 10 subjects shall receive dosage B of investigational vaccine (0.25 ml of JAIVAC-1 containing 25µg PfMSP-1 19 and 25µg PfF2 formulated with adjuvant Montanide ISA 720) by intramuscular route on Days 0, 28 and 180 |
| Control Arm 2 | 5 subjects shall receive control vaccine (1 ml of Hepatitis B vaccine) by intramuscular route on Days 0, 28 and 180                                                                                                             |

### Cohort 3

|                      |                                                                                                                                                                                                                                |
|----------------------|--------------------------------------------------------------------------------------------------------------------------------------------------------------------------------------------------------------------------------|
| Test Arm 3    | 10 subjects shall receive dosage C of investigational vaccine (0.5 ml of JAIVAC-1 containing 50µg PfMSP-1 19 and 50µg PfF2 formulated with adjuvant Montanide ISA 720) by intramuscular route on Days 0, 28 and 180 |
| Control Arm 3 | 5 subjects shall receive control vaccine (1 ml of Hepatitis B vaccine) by intramuscular route on Days 0, 28 and 180                                                                                                            |

Subjects, who discontinue participation before completing the study, and those who are prematurely withdrawn from the study for any reason, should be scheduled for a visit as soon as possible, at which time all of the assessments listed for the final visit will be performed.

## **7.2 Safety Assessments**

Safety assessment will begin with detailed medical history, record of concomitant medications, detailed physical examination and measurement of vital signs at each visit. The specific safety assessments for this study will include the following:

### **Clinical Safety Assessments**

*Information contained in this publication is the property of EVI and ICGEB and is confidential and will not be disclosed to third parties without written authorization from EVI and ICGEB. No part of this document may be reproduced, stored in a retrieval system or transmitted in any form or by any means -electronic, mechanical, recording or otherwise - without the prior authorization of EVI and ICGEB*

[figure not shown][figure not shown]

- Immediate reactogenicity (reactions recorded every 30 minutes till the first 3 hours after each vaccination, with emphasis on allergic /anaphylactic reactions)
- Local and systemic solicited reactogenicity measured from Day 0 (3 hours after vaccination to Day 14 after each vaccination)
- Any unsolicited adverse event up to 28 days after each vaccination
- Any Serious Adverse Event (SAE) occurring from the inclusion throughout the study till one-year (Day 365) after the first vaccination

### **Laboratory Safety Assessments**

- Laboratory assessments 28 days after each vaccination, in reference with the baseline before the first dose, by measuring the haematological and biochemical parameters.

### **7.2.1 Assessment of Immediate Reactogenicity**

Vital signs (including temperature, pulse, respiratory rate and blood pressure) will be recorded prior to each dose of the vaccine. After the administration of each dose of the assigned study vaccine, the subject will be monitored for any changes in vital signs every 30 minutes till 3 hours post-vaccination (with a window period of +/- 5 minutes for post-dose vital signs). Vital signs will be done after the subject has been resting quietly for at least 5 minutes. BP will be taken in the supine position. Appropriate medical treatment will be readily available at the study site to manage any adverse event with special emphasis on allergic/ anaphylactic reactions.

### **7.2.2 Assessment of Local and Systemic Reactogenicity (Solicited AEs)**

Local and systemic reactogenicity will be assessed for a period of 14 days following each vaccination i.e. from Days 0 to 14 for the first dose, Day 28 to 42 for the second dose and Day 180 to 194 for the third dose of the assigned study vaccine. This assessment of local and systemic signs and symptoms will be done based both on the subject diary card and investigator assessment as follows:

- For the first 14 days the subjects will be asked to record the local and systemic signs and symptoms (Solicited AEs) in their diary cards (pre-printed).
- In addition, 14 days after each vaccination (i.e. on Days 14, 42 and 194), the investigator will do an independent assessment of the local and systemic signs and symptoms.

#### **7.2.2.1 Solicited AEs by Subject Diary**

During the first 14 days (2 weeks) following each dose of the assigned study vaccine (Days 0 to 14, Day 28 to 42 and Day 180 to 194), subjects will be asked to record local and general signs and symptoms (Solicited AEs) using pre-printed diary cards, thermometer, and small ruler.

Solicited AEs to be reported by the subject are pre-printed on the diary cards and consist of the following:

- Local Reactogenicity (at the injection site) - pain, swelling, redness, induration and limitation of arm motion abduction at shoulder

*Information contained in this publication is the property of EVI and ICGEB and is confidential and will not be disclosed to third parties without written authorization from EVI and ICGEB. No part of this document may be reproduced, stored in a retrieval system or transmitted in any form or by any means -electronic, mechanical, recording or otherwise - without the prior authorization of EVI and ICGEB*

[figure not shown][figure not shown]

- Systemic Reactogenicity (systemic signs) - fever (axillary temperature) or systemic symptoms - headache, malaise, myalgia, arthralgia, nausea and vomiting.
- The investigator will review the subject diary cards and transcribe the data on solicited AEs on to the CRF on Days 7, 14, 35, 42, 187 and 194.
- The above-mentioned local and systemic symptoms and signs will be graded on the pre-printed diary card by the subject or the investigator as specified in the diary card instructions and based on Table 2: Scoring of Severity of Local Solicited Adverse Events and Table 3: Scoring of Severity of Systemic Solicited Adverse Events.

#### ***7.2.2.2 Solicited AEs by Investigator's Assessment***

The Investigator will do an independent assessment of the local and systemic signs and symptoms 14 days after each vaccination (i.e. on Days 14, 42 and 194),

- During these visits, the investigator will perform a complete physical examination (including general examination for temperature, lymphadenopathy and any other local or systemic signs and symptoms).
- In addition, the investigator will specifically check for the presence of a nodule (10) at the injection site. The size and outcome of the nodule (if any) will be recorded on the CRF pages, as well as the size, localisation and outcome of the local lymph nodes.
- The investigator will independently evaluate the subjects for solicited AEs on Days 14, 42 and 194.
- The above-mentioned local symptoms and signs (solicited AEs) will be graded on the CRF by the Investigator on Days 7, 14, 35, 42, 187 and 194 as per Table 2: Scoring of Severity of Local Solicited Adverse Events and Table 3: Scoring for Severity of Systemic Solicited Adverse Events

#### ***7.2.2.3 Assessment of Severity of Solicited Adverse Events***

Criteria for severity ranking for solicited AEs are given in Table 2 (11)-13) and Table 3 (11), 14) below. For events measured with continuous variables such as fever or diameters, the severity grades are provided for completeness. The investigator will report the highest measured value and the corresponding severity grade in the CRF.

*Information contained in this publication is the property of EVI and ICGEB and is confidential and will not be disclosed to third parties without written authorization from EVI and ICGEB. No part of this document may be reproduced, stored in a retrieval system or transmitted in any form or by any means -electronic, mechanical, recording or otherwise - without the prior authorization of EVI and ICGEB*

[figure not shown][figure not shown]

**Table 2: Scoring of Severity of Local Solicited Adverse Events**

| Pain at injection site                                      | Score/Grade |
|--------------------------------------------------------------------|--------------------|
| Absent                                                             | 0                  |
| Painful on touch                                                   | 1                  |
| Painful when limb is moved                                         | 2                  |
| Spontaneously painful or painful at rest                           | 3                  |
|                                                                    |                    |
| Swelling, Redness, Induration                               | Score/Grade |
| Absent                                                             | 0                  |
| Longest diameter: <25 mm                                           | 1                  |
| Longest diameter: $\geq 25$ mm to < 50mm                           | 2                  |
| Longest diameter: $\geq 50$ mm                                     | 3                  |
|                                                                    |                    |
| Limitation of arm motion abduction at shoulder              | Score/Grade |
| Angle of voluntary arm abduction is $180^\circ$                    | 0                  |
| Angle of voluntary arm abduction is $> 90^\circ$ but $< 120^\circ$ | 1                  |
| Angle of voluntary arm abduction is $> 30^\circ$ but $< 90^\circ$  | 2                  |
| Angle of voluntary arm abduction is $\leq 30^\circ$                | 3                  |

*Information contained in this publication is the property of EVI and ICGEB and is confidential and will not be disclosed to third parties without written authorization from EVI and ICGEB. No part of this document may be reproduced, stored in a retrieval system or transmitted in any form or by any means -electronic, mechanical, recording or otherwise - without the prior authorization of EVI and ICGEB*

[figure not shown][figure not shown]

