### 7.2.5 Assessment of Severity for all Unsolicited Adverse Events (including any Serious Adverse Events)

The Investigator will record, report and grade the following unsolicited AEs on the Adverse Event CRF pages, using medical language and as per Table 4: Scoring for severity of systemic unsolicited Adverse Events:

*Information contained in this publication is the property of EVI and ICGEB and is confidential and will not be disclosed to third parties without written authorization from EVI and ICGEB. No part of this document may be reproduced, stored in a retrieval system or transmitted in any form or by any means -electronic, mechanical, recording or otherwise - without the prior authorization of EVI and ICGEB*

[figure not shown][figure not shown]

- All unsolicited adverse events that occurred during the first 28 days following each dose of the vaccine, and
- All Serious Adverse Events during the entire study period (from study inclusion till last follow-up visit)

| Table 4: Scoring for severity of systemic unsolicited Adverse Events |                    |
|-----------------------------------------------------------------------------|--------------------|
| Unsolicited Adverse Event Characteristics                            | Score/Grade |
| Sign or symptom present, but easily tolerated                               | 1                  |
| Discomforting enough to interfere with normal activities                    | 2                  |
| Disabling, incapacitating with inability to perform usual activity          | 3                  |

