## 8 SAFETY MONITORING

### 8.1 Introduction

The collection, recording, assessment and reporting of adverse events (AE) and serious adverse events (SAE) represent the core activities for the safety evaluation. These activities are under the direct responsibility of the Investigator.

The recording of adverse events is an important aspect of study documentation as the evaluation of the safety of three (3) intramuscular injections of the investigational vaccine (JAIVAC-1 – Montanide ISA 720 malaria vaccine) in comparison with that of the control vaccine (Hepatitis B vaccine) is the primary objective of this study. The procedure for evaluation of immediate reactogenicity, solicited adverse events and unsolicited adverse events is described Section 7. The investigator is responsible for the detection and documentation of events meeting the definition of an adverse event (AE) or a serious adverse event (SAE) as provided in Sections 8.4 and 8.5 of this protocol. This includes the evaluation of its seriousness, its severity, and the causal relationship to the investigational vaccine and/or concomitant therapy.

At each visit, the investigator will assess whether any AE including laboratory abnormalities has occurred. The investigator shall inquire for unsolicited AEs with non-suggestive questions to the subject at each study visit. The investigator shall attempt to establish a diagnosis of the event based on signs, symptoms and/or other clinical information. The diagnosis shall be recorded as the AE and/or SAE and not the individual symptoms.

If a laboratory abnormality or other abnormal assessment meets the definition of an AE or SAE, the Adverse Event or Serious Adverse Event Form shall be completed as appropriate. A diagnosis, if known or clinical signs and symptoms if diagnosis is unknown, rather than the laboratory abnormality shall be reported. If no diagnosis is known and clinical signs and symptoms are not present, then the abnormal finding shall be recorded. The subject shall be observed and monitored carefully until the AE resolves, the condition stabilises or its cause is identified completely. The investigator is responsible for ensuring that follow-up includes any supplemental investigations that may be indicated to elucidate the nature and/or the cause of the event.

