### 8.4.2 Reporting of Adverse Events

To ensure subject safety, every AE, regardless of suspected causality, occurring after the subject has received the first dose of the vaccine till 28 days after the subject has received each dose of the vaccine will be reported. Information about all adverse events, whether volunteered by the subject, discovered by investigator questioning, or detected through physical examination, laboratory test or other means, will be collected and recorded on the Adverse Event Case Report Form and followed as appropriate. Thus, AEs will be collected through both solicited and unsolicited means and subsequently coded in tabular form using the latest version of MedDRA Adverse Event Dictionary. The subjects will be encouraged to report signs, symptoms, and any changes in health to the Investigator. Severity of each AE will be determined by the staff based on observation and questioning of the subjects. The Investigator will judge the relationship of the event to the study treatments.

Adverse events occurring before the subject has signed the informed consent as well as those which occur in the screening period are recorded on the Medical History. Abnormal laboratory values or test results constitute adverse events if they are not a part of any specific diagnosis, induce clinical signs or symptoms, require any action to be taken or any intervention to be made, and are considered as clinically significant. Such clinically significant abnormal lab values will be recorded on the Adverse Events Case Report Form under the signs, symptoms or diagnosis associated with them and will be followed till resolution or stabilization of the same.

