## 11.5 Analysis Methods

### 11.5.1 Statistical Model, Hypothesis Testing and Tests

No statistical hypothesis can be set up for the safety and immunogenicity data as sample size is limited. The analysis shall be descriptive as the sample size does not allow any comparison between groups. Categorical Variables will be summarised by vaccine groups as frequency, percentages and 95% confidence interval. Continuous Variables other than titers and Concentrations will be summarised by vaccine groups as Mean, SEM, Median, Minimum, Maximum, inter-quartile range/range. The proportion of subjects that received three doses without experiencing grade 3 adverse events will be estimated by Exact Binomial proportion (Proportion and 95% confidence interval).

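### Table 2 gives no grade to arm abduction of 120 to under 180 degrees, or to exactly 90, so mild limitation can be left ungraded or scored inconsistently

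*Supplement*

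**What the plan says.** **Abduction item.** Section 7.2.2.1 lists limitation of arm abduction at the shoulder among the solicited local events. Section 4.6.1 makes local reactogenicity part of the primary endpoint. Section 7.2.2.2 has the investigator grade these events on the CRF using Table 2, whose four rules, in degrees, are:

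- grade 0: "Angle of voluntary arm abduction is $180"
- grade 1: "Angle of voluntary arm abduction is $> 90^\circ$ but $< 120"
- grade 2: "Angle of voluntary arm abduction is $> 30^\circ$ but $< 90"
- grade 3: "Angle of voluntary arm abduction is $\leq 30"

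For events measured on a continuous scale, section 7.2.2.3 asks the investigator to report the highest value measured together with its grade. Section 4.5 leaves investigators, assessors and data analysts unblinded. Section 11.5.1.2 plans binomial proportions with 95% confidence intervals, by vaccine group, for local and systemic reactions.

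**Laboratory abnormalities.** Section 8.1 says: "If no diagnosis is known and clinical signs and symptoms are not present, then the abnormal finding shall be recorded". Section 8.4.2 makes an abnormal value an adverse event through a list of conditions that includes inducing signs or symptoms and ends "require any action to be taken or any intervention to be made, and are considered as clinically significant". Unsolicited events are graded by function. Grade 3 in Table 4 is "Disabling, incapacitating with inability to perform usual activity", and section 8.4.4 is similar. Section 11.5.1 then plans one named summary: "The proportion of subjects that received three doses without experiencing grade 3 adverse events will be estimated by Exact Binomial proportion".

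**The concern.** A severity scale should give every possible observation exactly one grade. The abduction item does not, and its main gap lies between no limitation and the mildest graded limitation. An assessor who sees 150 degrees cannot follow the table. He or she must leave the grade blank, call it grade 0 or call it grade 1, and the last two differ on whether a reaction occurred. The assessors know the allocation, and comparing safety with the control vaccine is a primary objective (section 3.1). That discretion is therefore open to bias, and in arms of 10 and 5 a single subject is visible in the result.

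Re-grading later from recorded angles is not assured. For abduction the highest angle is the least severe one, so section 7.2.2.3 read literally would store the wrong extreme. The tools that section 7.2.2.1 names for subjects are a thermometer and a small ruler, neither of which measures an angle.

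The laboratory point is separate and secondary. If an abnormality without symptoms is recorded as an adverse event, no printed scale allows it to reach grade 3, whatever its size.

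**Working it through.** The plan states no figure to reproduce: section 11.1.1 says that no formal sample size calculation was made.

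**1. Coverage of the abduction scale.** Each whole degree from 0 to 180 (181 values) is assigned by the Table 2 rules.

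| Rule | Whole degrees | Count |
|---|---|---|
| Grade 3, at most 30 | 0 to 30 | 31 |
| Grade 2, over 30 and under 90 | 31 to 89 | 59 |
| Grade 1, over 90 and under 120 | 91 to 119 | 29 |
| Grade 0, exactly 180 | 180 | 1 |
| **Graded** | | **120** |
| **No grade** | 90, and 120 to 179 | **61** |

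Check: 181 − 120 = 61 = 1 + 60. No value receives two grades. On the continuous scale the main gap is 180 − 120 = 60 degrees, plus the single point 90.

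**2. Where the gaps lie.** The gap from 120 to under 180 is between grades 0 and 1, so it can change whether a reaction is counted. The point 90 is between grades 1 and 2, so it affects only the split between those grades. Neither adjoins grade 3.

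**3. The other numeric scales.** Applying the same test to the diameter scale (Table 2) and the fever scale (Table 3) gives exactly one grade for every value tried, reading absent as a diameter of zero. Only abduction has gaps.

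**4. Effect of one subject in an arm of 10.** For x events in n subjects, the exact (Clopper-Pearson) 95% limits are: lower = 2.5% quantile of Beta(x, n − x + 1); upper = 97.5% quantile of Beta(x + 1, n − x).

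- x = 0: lower 0; upper = 1 − 0.025^(1/10) = 1 − 0.6915 = 30.8%.
- x = 1: lower = 1 − 0.975^(1/10) = 0.3%; upper = 44.5%.

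One mild limitation counted or not therefore moves the result between 0/10 (0 to 30.8%) and 1/10 (0.3 to 44.5%).

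**5. Laboratory events.** Read side by side, section 8.1 records an abnormality that has no signs or symptoms, while section 8.4.2, if its conditions are cumulative, does not. Once such an event is recorded, Table 4 and section 8.4.4 require disability for grade 3, which an event without symptoms cannot meet. Appendix B gives reference ranges and Appendix B-1 gives entry limits; neither grades severity. If one subject in an arm of 10 had such an event, counting it or not as grade 3 moves the proportion without grade 3 between 9/10 (55.5 to 99.7%) and 10/10 (69.2 to 100%).

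**The case against.** The strongest reply is that little follows from the gap.

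- Section 11.5.1.2 counts reactions without mentioning grade. Because grade 0 is reserved for exactly 180 degrees, 150 degrees is arguably already a reaction. This is a fair reading, but the section does not define when a local event counts, so the choice still rests with the grader.
- If the angle itself is recorded, grades can be derived later. This holds only if the angle is measured and the most limited value kept, which the text does not secure.
- The diary card instructions, which section 7.2.2.1 also cites for grading, are not among the documents and might close the gap. They would not mend Table 2, to which section 7.2.2.2 sends the investigator.
- No escalation or discontinuation rule in sections 5.4.4 or 8.2 depends on grade. This stands: the gap triggers no wrong decision by rule.
- The share of degrees without a grade is not a share of events. This also stands. The documents give no distribution of angles.

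On the laboratory side, biological safety is tabulated as raw values and against normal ranges (section 11.5.1.3), so a large rise without symptoms would still be seen. Section 8.4.1 counts an abnormal laboratory finding among adverse events, so the list in section 8.4.2 may be loose drafting rather than a real restriction. A numeric grading rule may also sit in the separate SAP or laboratory manual, neither of which is among the documents. These points make the laboratory matter secondary, but the two sections still need reconciling.

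**Conclusion.** The abduction item in Table 2 is a defective stated rule, not a detail left to another document. It leaves 61 of 181 whole-degree values without a grade. As a result, mild limitation of a primary-endpoint event can be left ungraded, or scored inconsistently as grade 0 or grade 1 by unblinded assessors. The effect is on any-grade and grade 1 and 2 counts. One subject in an arm of 10 moves the observed proportion by 10 percentage points and the upper confidence limit from 30.8% to 44.5%. This assumes that angles in the gap occur and that graders differ; how often cannot be judged from the documents.

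A reader might infer that the severity scales in general are incomplete, or that the graded safety results will be wrong. The documents do not support either: the fever and diameter scales are contiguous, and the grade 3 band for abduction is complete, so this gap cannot alter the grade 3 proportion. A reader might also infer that laboratory toxicity would be hidden, which the separate laboratory tabulations contradict. What remains there is narrower: on the printed scales, the proportion without grade 3 adverse events may be overstated if a serious laboratory abnormality without symptoms occurs.

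**What to change.** Before first vaccination:

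1. Make the abduction bands in Table 2 contiguous, so that every angle from 0 to 180 has exactly one grade. One way that keeps the existing cut-points is to extend grade 1 up to, but not including, 180 and assign 90 to one side. The sponsor should confirm the cut-points.
2. In section 7.2.2.3, state that for abduction the smallest angle is recorded with its grade.
3. Secondary: reconcile section 8.4.2 with section 8.1, so that a clinically significant laboratory abnormality without symptoms is recorded as an adverse event. State how such events are graded, or cite the document that does so, and say whether they enter the grade 3 summary.

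The cost is a short edit to Table 2 and to sections 7.2.2.3 and 8.4.2, with matching changes to the diary card and CRF. A laboratory grading rule is added work only if none already exists in the SAP or laboratory manual. Sample size and visits are unchanged. Grades are assigned at visits, so a later analysis plan cannot reliably restore a limitation that was never graded or measured.
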